#### Ethical concerns and consent

Ethics approval for this study was obtained from the UNSW Human Research Ethics Committee. Participants provide written consent online; the revocation of consent form is also available online.

### Intervention and control

Volunteers responding to the invitation are required to register online by providing consent, and completing the pre-study survey and the tutorial about *Healthy.me*.

The control and intervention arms of the trial run concurrently, meaning that the randomly allocated participants of the trial are exposed to the same influenza season and the same background of public health messaging. The only difference between the 2 arms is exposure to the intervention. Whilst there are clear annual differences in flu and vaccination rates, our study should detect if in a given year we are able to change consumer behaviour. It is likely that in different years the degree of effect will differ, and only long term and longitudinal studies would help us understand the underlying trend. Such studies would be contemplated after strong evidence from this study that the intervention in principle is capable of impacting behaviour in a single season.

#### Description of intervention

The intervention in this trial is a web-based PCHMS called *Healthy.me*, which consists of the following features (Figure 2):

**Figure 2 F2:**
[figure not shown]
**Features of *Healthy.me *(^© ^University of New South Wales, 2009-2012)**.

1. Personal Record: Allows for self-recording of medical test results and health measurements (not available to participants in this study).

2. Pillbox: Allows for self-recording of current medications and medication adherence.

3. Schedule, to-do list and reminders: An online schedule to self-record and keep track of health-related appointments, to-do items, which sends email reminders.

4. Team: A feature that allows the self-recording of clinical and non-clinical personnel looking after one's health.

5. Journeys: Consumer-specific care pathways that provide knowledge in an actionable way. A feature that describes the different stages in the management of health conditions that can be used to personalise other PHR sections in the system, and provides advice on what to expect and how to prepare for each stage. (Participants in this study had access to an influenza vaccine journey).

6. Social features for this study included: (i) a profile for each member to store and customise their personal information, (ii) the ability to send and receive messages with other members on *Healthy.me*.

Studies suggest that by addressing both knowledge-based (e.g. lack of awareness) and system-based (e.g. inconvenience) barriers in accessing health services, patients and consumers are more likely to uptake preventative health measures, such as influenza vaccination [6]. Our PCHMS is designed to address both knowledge-based and system-based barriers faced by consumers when accessing and utilising health services.

The PCHMS thus integrates a number of tools to address knowledge and system barriers that influence consumers' engagement with health services. Our PCHMS contains a PHR, as well as online social networking mechanisms that allow participants to interact with healthcare professionals at the service provider and other consumers, and additional tools to support consumer decision making and subsequent task management. In addition, it is integrated with consumer-specific care pathways (called "journeys") that provide knowledge in an actionable way. For example, at the point that a consumer encounters advice to seek influenza vaccination, they are immediately able to book an appointment with a medical practitioner, or set themselves a reminder.

The PCHMS was previously tested in a small trial with women undergoing in-vitro fertilisation (IVF), to demonstrate system usability and acceptance. Interview data from this trial provided evidence that the system positively impacted consumer advice-seeking behaviours [7].

The influenza vaccine journey in *Healthy.me *was iteratively developed and validated in consultation with the University Health Service (i.e. university's general practice) (Figure 3). It utilises government-endorsed evidence-based consumer education material that had been tested in the previous year to inform the UNSW community about seasonal influenza and pandemic H1N1 influenza [8-11].

**Figure 3 F3:**
[figure not shown]
**Top page of *Healthy.me *influenza vaccine journey (^© ^University of New South Wales, 2009-2012)**.

#### Intervention group and exposure

The period of access to *Healthy.me *will vary depending on the date of participant registration. During the study *Healthy.me *will provide participants in the intervention group with information and forward email reminders about influenza, indications for vaccination, as well as an email link to the University Health Service for participants to book an appointment for influenza vaccination or other medical concerns, should they wish to use that service (Figure 4).

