**Figure 1 F1:**
[figure not shown]
**Overview of RCT process**.

• Participants randomised to the *intervention *group will have immediate access to *Healthy.me *from the date they are recruited in addition to health care of usual standard.

• Participants randomised to the *control *group will receive usual care. They will be allocated to a waiting list and delayed to use *Healthy.me *by approximately six months.

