### Outcome measures

Table 2 outlines the primary and secondary outcome measures in this study. Participants in control and intervention groups who are analysed for primary outcome will have completed the post-study survey and/or provided influenza vaccination status by de-identified clinical audit. Participants in intervention group who had the opportunity to use *Healthy.me *but did not do so will be included in the primary analysis. Participants who met the exclusion criteria or whose influenza vaccination status was unavailable at study completion will be excluded.

**Table 2 T2:** Primary and secondary outcome measures collected at different time points

Outcome measure	Measurement timepoints & methods
*Primary outcome*	
Proportion of participants obtaining influenza vaccination during the study	• Study completion^1 ^(via self-reports and clinical audit)
*Secondary outcome*	
Proportion of participants visiting the University Health Service during the study	• Study completion^1 ^(via self-reports and clinical audit)
*Ancillary outcomes*	
Proportion of participants experiencing symptoms of influenza-like illness ^2 ^(ILI) during the study	• Monthly from study commencement in May to October 2010 (via self-reports)
Proportion of participants using medications or remedy due to ILI symptoms ^2^	• Monthly from study commencement in May to October 2010 (via self-reports)
Proportion of participants visiting a healthcare professional due to ILI symptoms ^2^	• Monthly from study commencement in May to October 2010 (via self-reports)
Proportion of participants experiencing impairment in work or study due to ILI symptoms ^2^	• Monthly from study commencement in May to October 2010 (via self-reports)
Number of days absent from work or study due to ILI symptoms (per participant)	• Monthly from study commencement in May to October 2010 (via self-reports)
Reasons for receiving (or not receiving) influenza vaccine	• Study completion^1 ^(via self-reports)
Patterns of usage and feedback of PCHMS	• Study completion^1 ^(via automatic system logs, data entered by participants into PCHMS, and self-reports)

^1^Estimated end of average respiratory disease and influenza season in Southern Hemisphere (i.e. October 2010, six months from study commencement)

^2^Defined by case definitions of influenza (fever with cough or a sore throat) issued by NSW Health and Centers for Disease Control and Prevention (CDC) as of 26 March 2010

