### Study procedure

Table 3 summarizes participant procedures in the study. The duration of the study is expected to be six months from May 2010 to October 2010.

**Table 3 T3:** Stages of study procedure

Stage of study	Procedure
Online registration	- Participant registration, study consent and Healthy.me tutorial (self-completed online)

Baseline	- Pre-study survey (self-completed online)
	- Data from de-identified clinical audit from previous 12 months: electronic extraction (collected post-study)

Follow-up procedures	- Monthly one-minute surveys (self-completed online)
	- Post-study survey (self-completed online)
	- Patterns of *Healthy.me *use (computer logs and data entered by participants)
	- De-identified clinical audit at study completion: electronic extraction (collected post-study)

Email will be the primary channel to communicate with participants for study information and reminders about survey completion. From the time participants are recruited until study completion, all participants (control & intervention) will receive an email in the first week of each month to complete a one-minute survey about their health in the past month. At study completion, all participants will receive an email asking them to complete a post-study survey. Two follow-up emails five days apart from each other will be sent to remind those who have not completed each survey to ensure the completeness of data collection.

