## Limitations

There are several potential limitations in this study:

• *Number of eligible participants*: Recruitment may be affected by an overlap between the start of respiratory season in Australia and the student examination period, potentially affecting student and staff availability and interest to participate in research studies. The number of participants meeting exclusion criteria at study completion might be significant because staff members are eligible for free influenza vaccination offered by UNSW one week prior to study commencement. As free vaccination would be a confounder if included in this trial, we explicitly ran our campaign independently of the university program.

• *Self-reports of influenza vaccination and health service utilisation*: Since clinical audits will only be conducted at the University Health Service, and not other GP practices, the study is dependent on participants' self-reporting of their influenza vaccination and health service utilisation. Self report has shown to be acceptably accurate in numerous studies examining days of absence [34], influenza symptoms, and vaccination status for diverse patient cohorts [20,33,35-38]. We will minimise the risk of recall bias by conducting short one-minute monthly follow-up surveys on the first week of each month.

• *Representative of general healthcare consumers*: The study may be more appealing to consumers who are interested or literate in computers, the Internet, or health-related topics. These participants may be more enthusiastic about health and the Internet than the general health consumer population. In addition, participants from a university setting are more likely to be open and positive to new research ideas and willing to participate in research studies. Further, generalisability of findings could be limited by recruiting participants from one university.

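### Rolling entry with a common October 2010 close gives participants unequal vaccination windows, which neither the planning rates nor the named covariates take into account

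*Protocol article*

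**What the plan says.** All references are to the protocol article.

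- **Start of exposure.** The design description gives the intervention group access "from the date they are recruited in addition to health care of usual standard". *Intervention group and exposure* adds that the length of access "will vary depending on the date of participant registration".
- **End of the outcome.** The primary outcome in Table 2 is "Proportion of participants obtaining influenza vaccination during the study", read at study completion. The table's footnote fixes that as one calendar point: "i.e. October 2010, six months from study commencement". *Study procedure* agrees: "The duration of the study is expected to be six months from May 2010 to October 2010".
- **Follow-up.** Monthly contact is individual at the start and common at the end: "From the time participants are recruited until study completion, all participants (control & intervention) will receive an email".
- **Planning rates.** *Sample size considerations* uses 15% versus 25%, a two-sided 5% level, 80% power and about 10% dropout, giving 300 per group. The control rate is informed by an audit showing 16% vaccinated between 5 March and 5 November 2009, and by literature giving 18 to 30% in a year. The effect size comes from a review of reminder systems.
- **Analysis.** *Primary analysis* uses a χ² test, then a sequential logistic regression. Step 1 holds the baseline characteristics, with a pointer to Table 1, plus contact with children and past influenza vaccination. Table 1 as printed is the eligibility table. Entry date is not named anywhere.

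**The concern.** A participant who registers at the opening has about six months in which to be vaccinated. One who registers later has less time, and that time falls later in the influenza season. The χ² test counts both alike. If vaccination accrues over time in both arms, shorter windows lower both proportions and narrow the gap between them. The sample size takes one pair of rates, supported by windows of eight months and a year, and its only stated allowance is for dropout.

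What is at stake is how the result will be read. The trial is meant to show whether "the intervention in principle is capable of impacting behaviour in a single season". If the observed difference is smaller than planned, a reader who sees only the pooled proportions cannot tell a weak intervention from short windows.

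**Working it through.** **Inputs.** From the article: 15% and 25%, two-sided 5%, 80% power, 10% dropout, 300 per arm, study length six months. Assumed, because the article does not give them: 15% and 25% apply to a full six-month window; registration is uniform over the first R months; the vaccination hazard is constant in each arm.

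**Step 1: reproduce the plan's figure.** With p̄ = 0.20,
m = [1.96·√(2·0.20·0.80) + 0.842·√(0.15·0.85 + 0.25·0.75)]² / 0.10² = 250 per arm.
With the continuity correction, n = (m/4)·[1 + √(1 + 4/(m·0.10))]² = 270. Then 270/0.90 = 300 per arm, 600 in total. The stated figure is matched exactly, and after dropout no margin is left for shorter windows.

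**Step 2: hazards.** Control: −ln(0.85)/6 = 0.0271 per month. Intervention: −ln(0.75)/6 = 0.0479 per month.

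**Step 3: average over entry dates.** A person with t months left is vaccinated with probability 1 − exp(−h·t). With t uniform between 6 − R and 6, the mean is
1 − [exp(−h(6 − R)) − exp(−6h)] / (h·R).

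**Step 4: power.** At 270 evaluable per arm, invert the continuity correction to get m, then power = Φ{[d·√m − 1.96·√(2p̄(1 − p̄))] / √(p₁(1 − p₁) + p₂(1 − p₂))}. For R = 2: d = 0.0863, m = 247.3, p̄ = 0.1697, so (1.357 − 1.041)/0.527 = 0.60 and Φ = 0.73.

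| Registration lasts | Control | Intervention | Difference (points) | Power | Per arm for 80%, after dropout |
|---|---|---|---|---|---|
| 0 months | 15.0% | 25.0% | 10.0 | 80% | 300 |
| 1 month | 13.8% | 23.2% | 9.3 | 77% | 325 |
| 2 months | 12.7% | 21.3% | 8.6 | 73% | 355 |
| 3 months | 11.5% | 19.3% | 7.9 | 68% | 393 |
| 4 months | 10.2% | 17.3% | 7.1 | 62% | 442 |

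**Step 5: vary the hazard assumption.**
- *Front-loaded uptake.* If the hazard decays exponentially from the study start with a time constant of two months (assumed), two months of registration gives 9.4% versus 16.0%, a difference of 6.6 points, and 58% power.
- *Prompt effect.* If the system acts soon after entry and the full 10 points are kept, two months of registration gives 12.7% versus 22.7%. Power without continuity correction then rises from 83% to 86%, because the proportions are lower.

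**Step 6: would an early registration cut-off help?** Use the constant-hazard model and suppose registration is stopped at two months. If 600 would have taken three months, 270 × 2/3 = 180 evaluable per arm remain and power is 53%, against 68% if left open. If 600 would have taken four months, 135 per arm remain and power is 41%, against 62%. The smaller sample costs more than the wider difference gains.

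**The case against.** Much of the case on the other side stands.

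- **No bias between arms.** The arms run concurrently and allocation is sequential in blocks of 2, 4 and 8, so entry dates are closely balanced. The χ² test remains a valid comparison.
- **No broken promise.** A reader might infer that a six-month effect per participant is claimed. It is not: six months describes the study calendar and the control group's delay. The variable access period is openly disclosed.
- **The window is defined.** A reader might say that the exposure period is undefined. Table 1 excludes from analysis anyone vaccinated in 2010 before enrolment, and Table 2 closes the outcome in October 2010. Together these make the counted window own enrolment to October 2010.
- **No closing date is no defect.** This is a condensed article, and an accrual schedule commonly sits in the full protocol. Nothing in the text supports registrations as late as September. The *Limitations* remark that "Recruitment may be affected by an overlap between the start of respiratory season in Australia and the student examination period" concerns participant numbers, and does not predict late registration.
- **Dilution is conditional.** The article says that a user who meets vaccination advice can book at once, which makes a prompt effect plausible. In that case there is no loss.

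What the objection does not remove is that the windows are unequal by design, the planning rates were not matched to them, and the analysis as described would not show whether this mattered.

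**Conclusion.** The point holds as a modest one about power and interpretation. Unequal windows follow directly from the stated entry and closing rules. The planning rates rest on longer periods with no stated allowance, and the covariates named for Step 1 omit entry date.

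The size can only be given as a range, because the accrual period and the speed of the effect are not stated. Under constant hazard and uniform entry, the planned 10 points and 80% power become 8.6 points and about 73% for two months of registration, and 7.1 points and about 62% for four. Front-loaded uptake would make the loss larger, and a prompt effect on entry would remove it. A lower control rate alone does not cost power; the loss arises only if the difference shrinks with it. The documents do not support saying that the effect is diluted as a matter of fact, or that late registrants cannot show an effect.

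**What to change.** 1. Name registration date as a baseline covariate at Step 1 of the sequential logistic regression. It is fixed before allocation and the online registration system already records it.
2. Report the difference between arms descriptively by month of registration, without testing, so that a result shaped by short windows can be recognised.
3. State in *Sample size considerations* that the 80% power assumes 15% versus 25% over the windows participants actually have, and check those rates against the expected registration period.

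All three cost only wording and one extra table. The covariate should not be oversold: simulation under these assumptions shows no power gain with constant hazard and about 1.5 to 2 percentage points with front-loaded uptake. It also leaves the unadjusted χ² test as it is. The main benefit is interpretability. Do not add an early registration cut-off for this reason, since it would lose more power through sample size than it restores.

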**Figure 4 F4:**
[figure not shown]
**Booking appointment with University Health Service on *Healthy.me *(^© ^University of New South Wales, 2009-2012)**.

The intervention will not modify in any way the standard procedures of healthcare provision by the University Health Service. Only administrative staff at the practice would receive requests for appointments facilitated by *Healthy.me*; no clinical staff assessing patient outcomes and/or administrating influenza vaccination would receive these appointment requests.

A pilot was conducted in a controlled university setting with three men and three women of different ethnic and cultural backgrounds and age groups, representative of the university student and staff population. Substantive issues on system usability, journey content, surveys, study protocol and advertisement material were resolved before recruiting UNSW students and staff to participate in their normal setting.

#### Control

Participants in the control group will receive delayed access to *Healthy.me *by approximately 6 months.

### Sample size considerations

The sampling unit is the participant and the unit of analysis is also the participant. A conservative estimate of 600 participants with 300 in each group is needed to detect a 10% difference in influenza vaccination rate between the control group (15%) and the intervention group (25%). This estimate is calculated at 5% level of significance, 80% power (two-sided test), with an anticipated participant dropout rate around 10% [12].

The effect size estimate is based on a review assessing the effectiveness of patient reminder systems in improving immunization rates, which can range from 5 to 20% [13]. The baseline rate estimate of influenza vaccination was informed by our audit conducted at the University Health Service, showing 16% of patients at the practice received FluVax or PanVax between 5/3/2009 to 5/11/2009. This estimate is also supported by literature reporting 18 to 30% of university students and healthy adults (18 to 49 years old) obtaining influenza vaccination in a year [14,15].

### Outcome measures

Table 2 outlines the primary and secondary outcome measures in this study. Participants in control and intervention groups who are analysed for primary outcome will have completed the post-study survey and/or provided influenza vaccination status by de-identified clinical audit. Participants in intervention group who had the opportunity to use *Healthy.me *but did not do so will be included in the primary analysis. Participants who met the exclusion criteria or whose influenza vaccination status was unavailable at study completion will be excluded.

**Table 2 T2:** Primary and secondary outcome measures collected at different time points

Outcome measure	Measurement timepoints & methods
*Primary outcome*	
Proportion of participants obtaining influenza vaccination during the study	• Study completion^1 ^(via self-reports and clinical audit)
*Secondary outcome*	
Proportion of participants visiting the University Health Service during the study	• Study completion^1 ^(via self-reports and clinical audit)
*Ancillary outcomes*	
Proportion of participants experiencing symptoms of influenza-like illness ^2 ^(ILI) during the study	• Monthly from study commencement in May to October 2010 (via self-reports)
Proportion of participants using medications or remedy due to ILI symptoms ^2^	• Monthly from study commencement in May to October 2010 (via self-reports)
Proportion of participants visiting a healthcare professional due to ILI symptoms ^2^	• Monthly from study commencement in May to October 2010 (via self-reports)
Proportion of participants experiencing impairment in work or study due to ILI symptoms ^2^	• Monthly from study commencement in May to October 2010 (via self-reports)
Number of days absent from work or study due to ILI symptoms (per participant)	• Monthly from study commencement in May to October 2010 (via self-reports)
Reasons for receiving (or not receiving) influenza vaccine	• Study completion^1 ^(via self-reports)
Patterns of usage and feedback of PCHMS	• Study completion^1 ^(via automatic system logs, data entered by participants into PCHMS, and self-reports)

^1^Estimated end of average respiratory disease and influenza season in Southern Hemisphere (i.e. October 2010, six months from study commencement)

^2^Defined by case definitions of influenza (fever with cough or a sore throat) issued by NSW Health and Centers for Disease Control and Prevention (CDC) as of 26 March 2010

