### Participants and setting

Table 1 outlines participant inclusion and exclusion criteria. The study will recruit students and staff members at UNSW who are fluent in English. Written material advertising the study outlines participant inclusion criteria, which are self-explanatory (i.e. age ≥ 18 and monthly access to Internet and email). Exclusion criteria are applied post-study. Hence, participants who self-identify as meeting inclusion criteria proceed to first providing informed consent before commencing the pre-study survey.

**Table 1 T1:** Eligibility criteria for participants

Inclusion criteria	Exclusion criteria
1. Aged 18 or above.	1. Participants who did not complete registration process [excluded before randomization].

1. Access to the Internet, and email at least on a monthly basis.	2. Participants who self-reported having obtained an influenza vaccination in 2010 prior to enrolment in the study [excluded from analysis].

	3. Participants who self-reported to be influenced by other participants during the study to obtain (or not obtain) influenza vaccination [excluded from analysis].

Participants engage in this trial online in their own space at their own time. All participants are required to complete online (i) a 5-10 minute pre-study survey; (ii) a monthly one-minute survey to collect their health symptoms and health service use; and (iii) a 5-10 minute post-study survey. Participants allocated to the *Healthy.me *group are also required to complete a five-minute mandatory online tutorial about system before commencing the study. Those who complete all study surveys will enter into a draw for $500 prize at study completion.

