#### Primary analysis

Differences in proportions of participants obtaining influenza vaccination during the study will be compared between waitlist and PCHMS groups. All intervention recipients who had the opportunity to use the PCHMS but did not do so will be included in the primary analysis. Differences in participant proportions between waitlist and PCHMS groups will be analysed using χ^2 ^test. Proportions will be reported with 95% confidence intervals.

Adjustments for baseline characteristics and potential confounders will be made through the use of sequential logistic regression [31]. Baseline characteristics (Table 1), and factors that may affect influenza vaccination collected at post study (i.e. contact with children during study, past history of influenza vaccine) will be entered at Step 1 of the regression; and group allocation (PCHMS vs. waitlist) will be entered at Step 2.

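### Survey non-responders can enter the primary analysis only through an audit of the one clinic the intervention books people into, so inclusion can depend on arm and outcome

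*Protocol article*

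**What the plan says.** Under Outcome measures, participants of either arm analysed for the primary outcome "will have completed the post-study survey and/or provided influenza vaccination status by de-identified clinical audit". The same paragraph adds: "Participants who met the exclusion criteria or whose influenza vaccination status was unavailable at study completion will be excluded".

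Under Data collection, the post-study survey is the instrument that collects vaccination status. The monthly surveys are described as covering symptoms, service use and impact on work or study. The audit is introduced there as a means of validating self-reports in a subset of participants.

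The Limitations section confirms how far the audit reaches: "Since clinical audits will only be conducted at the University Health Service, and not other GP practices".

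Under Intervention group and exposure, the intervention arm receives information, reminders, "as well as an email link to the University Health Service for participants to book an appointment for influenza vaccination". The second study hypothesis is that online scheduling raises use of the linked provider, and Table 2 makes UHS visits the secondary outcome.

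Under Sample size considerations, 300 per arm is planned for 15% versus 25%: "This estimate is calculated at 5% level of significance, 80% power (two-sided test), with an anticipated participant dropout rate around 10" per cent.

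**The concern.** A person who does not return the post-study survey can enter the primary analysis only if the UHS record supplies a status. Someone vaccinated at UHS can be recovered as an event. Someone vaccinated elsewhere, or with no UHS record, leaves both numerator and denominator. The trial itself expects UHS contact to be more frequent in the intervention arm, so the chance of recovery is linked to both arm and outcome.

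At stake is the primary comparison. If the system merely moved vaccinations to UHS without adding any, the rule could still produce a difference in its favour. If the system does work, the rule could enlarge the estimate. The audit is also given two roles: validation under Data collection, and substitute source of the primary outcome under Outcome measures. The document does not say how it classifies a UHS patient without a vaccination entry, or a person with no match.

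**Working it through.** **1. The plan's own figure.** Inputs from Sample size considerations: 15% versus 25%, two-sided 5%, 80% power, about 10% dropout.

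- n = [1.960·√(2·0.20·0.80) + 0.8416·√(0.15·0.85 + 0.25·0.75)]² / 0.10² = 249.98, so 250 per arm.
- With continuity correction: (249.98/4)·[1 + √(1 + 4/(249.98·0.10))]² = 269.6, so 270 per arm.
- For dropout: 270/0.9 = 300 per arm, 600 in total.

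The stated size reproduces and is not in dispute.

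**2. Model for the inclusion rule.** Let

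- p = true vaccination rate;
- m = survey non-response, taken as equal in both arms and unrelated to vaccination;
- s = share of vaccinated non-responders found in the UHS audit;
- u = share of unvaccinated non-responders whom the audit returns as not vaccinated.

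Observed rate = p(1−m+ms) / [p(1−m+ms) + (1−p)(1−m+mu)].

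The document gives p = 15% for control and about 10% dropout. It gives no value for s or u, and no non-response above 10%; these are assumptions.

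**3. No true effect (15% in both arms), s = 0.2 control and 0.6 intervention, u = 0.**

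| m | Control | Intervention | Spurious difference |
|---|---|---|---|
| 10% | 0.138/0.903 = 15.28% | 0.144/0.909 = 15.84% | +0.6 points |
| 20% | 0.126/0.806 = 15.63% | 0.138/0.818 = 16.87% | +1.2 points |
| 30% | 0.114/0.709 = 16.08% | 0.132/0.727 = 18.16% | +2.1 points |

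In people, at 10% non-response: 300·0.10·0.15 = 4.5 vaccinated non-responders per arm, of whom 4.5·0.2 = 0.9 (control) and 4.5·0.6 = 2.7 (intervention) re-enter.

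With s = 0.3 versus 0.7 the differences are again +0.6, +1.2 and +2.1 points. The two-sided rejection rate of a pooled two-proportion z-test on the expected numbers analysed is then 5.4%, 6.5% and 8.6%, instead of 5%.

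**4. Planned effect (15% versus 25%), s = 0.3 versus 0.7, u = 0.** The expected difference is 11.0 points at 10% non-response (15.42% versus 26.43%) and 13.6 at 30% (16.61% versus 30.23%), instead of 10.

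**5. If the audit also returns unvaccinated people.** With no true effect the bias vanishes when (1−m+ms)/(1−m+mu) is equal in the two arms. At m = 10%, s = 0.2 versus 0.6:

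- u = 0.3 in both arms: 14.86% versus 15.41%, +0.55 points. Equal recovery barely helps.
- u = 0.1 versus 0.3: 0.138/0.9115 = 15.14% versus 0.144/0.9345 = 15.41%, +0.27 points.
- u = 0.1 versus 0.5: 15.14% versus 0.144/0.9515 = 15.13%, about zero.

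**6. Power under an arm-neutral rule, 300 per arm.**

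| m | Survey status only (15% vs 25%, n = 300(1−m)) | Missing = not vaccinated (n = 300) |
|---|---|---|
| 10% | 0.83 | 0.82 (13.5% vs 22.5%) |
| 20% | 0.78 | 0.76 (12% vs 20%) |
| 30% | 0.73 | 0.70 (10.5% vs 17.5%) |

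**The case against.** The inclusion rule is worded identically for both arms, so any dependence on arm is indirect, through UHS use that is only hypothesised. That is right, and it is why the direction is expected rather than certain.

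At the only non-response figure in the document the effect is about half a point against a 10-point target, and reminder emails and a prize draw support completion. That stands and limits the severity.

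The UHS shares are assumed. The booking link also serves other medical concerns, so unvaccinated non-responders may be matched more often in the intervention arm too, which can cancel the bias (step 5). People who ignore survey emails may ignore booking emails as well: with s = 0.2 versus 0.4 and u = 0, the 10% figure halves to 15.56% − 15.28% = +0.28 points. Both points stand. They make the size uncertain; they do not make the rule neutral.

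Self-report alone is not free of trouble either: participants are unblinded and may respond or report differently by arm. That supports keeping the audit, as validation.

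Three stronger readings are tempting but not supported.

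- A reader might infer that intervention participants can be dropped for lacking an opportunity to use the system. The sentence reads "All intervention recipients who had the opportunity to use the PCHMS but did not do so will be included in the primary analysis": it keeps non-users in, and nothing excludes anyone for lack of opportunity.
- A reader might infer that abandoning the tutorial removes people from one arm. Participants and setting says the Healthy.me group "are also required to complete a five-minute mandatory online tutorial about system before commencing the study", while Intervention and control says volunteers "are required to register online by providing consent, and completing the pre-study survey and the tutorial about" the system, and Table 3 lists the tutorial under registration. These disagree on who takes it and when. But Table 1 lists no exclusion for it after allocation, and incomplete registration is an exclusion before randomisation.
- A reader might cite worst- and best-case bounds of 22.5% − 23.5% = −1 to 32.5% − 13.5% = +19 points at 10% missing. Any trial with these rates and this much missing data has those bounds; they do not come from the audit rule.

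**Conclusion.** The concern holds, at moderate severity. The protocol fixes a rule under which entry to the primary analysis can depend on both arm and outcome, and its own hypothesis on UHS use points towards a bias that favours the intervention. This is a stated rule, not a detail left to an analysis plan.

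Under the assumed 20% versus 60% shares, with no recovery of unvaccinated non-responders, the bias is small at the planned 10% non-response and becomes material only if response falls well short of plan. It could be near zero if unvaccinated UHS patients are also recovered more often in the intervention arm. The document does not fix the shares, the classification of audit matches or the response by arm, so neither sign nor size can be claimed with certainty.

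The tutorial inconsistency is a separate matter of wording.

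**What to change.** 1. Analyse participants as allocated, with primary vaccination status from the same source in both arms: post-study self-report.
2. Use the UHS audit for validation, the purpose given under Data collection, and for a sensitivity analysis that adds audit-only statuses. State how a matched patient without a vaccination entry and an unmatched person are classified.
3. Report the number of audit-only entries by arm, split by vaccinated and not vaccinated.
4. Add an analysis of all randomised participants without a pre-enrolment vaccination, with missing status counted as not vaccinated, or imputed using arm, baseline and monthly-survey data.
5. Reconcile Participants and setting, Intervention and control, and Table 3 on who takes the tutorial and when.

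The cost is wording and a little extra analysis. A few audit-only events leave the primary definition. No extra recruitment is needed at the planned dropout: power is about 82–83% with 300 per arm free of pre-enrolment vaccination. At 20% non-response it would be 76–78%.
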